### Interim analyses {21b}

An interim analysis will be conducted after half of the anticipated sample has been enrolled and completed their final visit. Statistical considerations for ending the trial prior to reaching the target enrollment will be based on the Haybittle-Peto stopping rules for the primary outcome
^
28
^.

The analysis will explore the primary outcome i.e., to determine the effect of adjunctive corticosteroids on all-cause mortality at 30 days after randomization in both the intention-to-treat (ITT) and per protocol (PP) participants. Cox regression will be used to test for differences in the rates of the primary outcome by randomization arm. The proportional hazards assumption will be evaluated graphically and using formal statistical tests. Kaplan-Meier survival curves will be constructed to display cumulative mortality over the 30-day follow-up period.

The results of this analysis will be shared with the trial’s Data Safety Monitoring Board (DSMB) and Trial Steering Committee (TSC) who will advise on continuation of the trial based on clear survival benefits or futility.

### Methods for additional analyses (e.g. subgroup analyses) {20b}

Secondary analyses will be conducted as for the primary analysis but adjusting for the confounding factors of gender, hospital location, age at randomization and any other confounder as deemed appropriate. Although randomization into the study is not stratified by any of the baseline characteristics, stratified analyses will be presented if there is significant evidence of interaction by any of the baseline variables.

The safety analysis will be based on the safety population, that is, all participants who received a study treatment.

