## Methods: Participants, interventions and outcomes

### Study setting {9}

The proposed study will be conducted within the Clinical Information Network (CIN), and five other hospitals. The CIN is a collaborative effort between KEMRI-Wellcome Trust Research Programme, Kenya Paediatric Association (KPA), Kenya’s Ministry of Health (MoH), and several county hospitals
^
17–
19
^. CIN, which commenced in 2013, initially sought to improve the care provided to in-patient children and sick new-borns through improving the collection and use of information obtained from routine medical records. At the onset of the COVID-19 pandemic, it expanded to the adult wards to conduct surveillance on severe acute respiratory illness (SARI) and now includes collection of routine data from adult wards. A total of 24 hospitals are currently part of the CIN. Use of de-identified routine data obtained from the CIN hospitals for observational research has been approved by the Kenya Medical Research Institute Scientific and Ethics Review Unit (KEMRI SERU).

The trial will recruit participants at the following 15 hospitals which are part of CIN: Bungoma County Referral Hospital, Busia County Referral Hospital, Embu Level 5 Teaching and Referral Hospital, HomaBay County Referral Hospital, Jaramogi Oginga Odinga Teaching and Referral Hospital, Kakamega County General Hospital, Kiambu Level 5 Hospital, Kisii Teaching and Referral Hospital, Kisumu County Hospital, Kitale County Referral Hospital, Machakos Level 5 Hospital, Mama Lucy Kibaki Hospital, Mbagathi County Hospital, Naivasha Level 5 Hospital and Nakuru County Referral Hospital (
Figure 1). Five other hospitals that are trial sites but are not part of CIN include Coast General Teaching and Referral Hospital, Kenyatta National Hospital, Kenyatta University Teaching and Referral Hospital, Kilifi County Hospital, and Moi Teaching and Referral Hospital, Eldoret (
Figure 1).

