### Sample size {14}

The primary hypothesis is that adjunct corticosteroid treatment will reduce mortality in the intervention arm by ~25% (relative measure). This is a conservative measure as the studies described in the background report relative risk reductions of between 33% and 61%. Observational data indicates 30% in-hospital mortality among based on data collected from CIN hospitals in the past one year and Kilifi County Hospital over a period of 5 years
^
24
^. We have made a conservative assumption that 30-day mortality in the control arm of the trial will be 20% and that 30-day mortality in the intervention arm will be 15%. Allowing for 5% loss to follow-up, a sample size of 1,090 patients per study arm (total 2,180 patients, ~ 390 deaths) will achieve statistical power of 85%, with a 2-sided type 1 error rate of 5%.

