## Assignment of interventions: allocation

### Sequence generation {16a}

Once eligibility has been confirmed and informed consent provided, all patients will be randomized to receive either:

a) Standard of care, OR,

b) Standard of care plus adjunctive low-dose corticosteroids for 10 days

The random allocation sequence will be computer-generated at the KEMRI-Wellcome Trust Research Programme according to a block randomization list of random block sizes for each site.

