### Concealment mechanism {16b}

At each site, printed and sealed sequential randomization cards will be used for treatment allocation. The envelopes will be numbered in a sequential order to prevent out of order randomization and each study site will have a unique set of randomization cards numbered from the first to the last.

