## Statistical methods

### Statistical methods for primary and secondary outcomes {20a}

The primary analysis will be an intention to treat analysis in which we will compare outcomes between all patients randomized to the two study arms, irrespective of whether they receive their allocated treatment. For the primary outcome of 30-day mortality, we will use the unadjusted hazard ratio determined from Cox regression to estimate the mortality rate ratio between the treatment groups. If we detect any imbalances in potential confounders at baseline (such as age, sex, severity of illness, study site), then an adjusted Cox model will be used. If losses to follow-up do occur, patients will be censored at time of last assessment. Kaplan-Meier survival curves will be constructed to display cumulative mortality over the 30-day follow-up period.

In the per-protocol analysis we will exclude patients stopping or pausing the study medication at any time point and those withdrawn from the trial.

Complete case analyses will be used for secondary endpoints. For all secondary endpoints, we will calculate unadjusted and adjusted estimates of the effect size and corresponding 95% confidence intervals using linear, logistic, or cox proportional hazards regression as appropriate. All analysis will be done using R (Version 4.4.2, R Foundation for Statistical Computing: Vienna, Austria)

For the immunology outcome, omics data such as proteomic and transcriptomic data generated will be processed in the R programming language as described in section 33. To find genes/proteins whose mean response has significantly changed over the first 72 hours, the processed data will be fitted in a multinomial mixed model predicting the possible outcomes, adjusting for relevant baseline characteristics. The expected outcomes are, survived versus died in the treatment and placebo arms.

To understand the biological response associated with survival, induced/repressed by the treatment, functional analysis of the significant genes/proteins will be explored using R packages such as Clusterprofiller, GSVA and fgsea.

Integrative approaches will be used on the cellular phenotyping, proteomic, transcriptomic, metabolomic data to elucidate the biological processes promoted/repressed by corticosteroid treatment that are associated with survival that could be targeted with additional intervention

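### Randomisation is blocked within site, so it is stratified by site; the protocol denies stratification and leaves site out of the primary Cox model, making the test slightly conservative if mortality differs between hospitals.

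*Protocol article*

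**What the plan says.** All places are in the protocol article.

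- **Sequence generation {16a}:** the allocation sequence is generated "according to a block randomization list of random block sizes for each site".
- **Concealment mechanism {16b}:** "each study site will have a unique set of randomization cards numbered from the first to the last".
- **Methods for additional analyses {20b}:** "Although randomization into the study is not stratified by any of the baseline characteristics", stratified analyses will still be shown where an interaction is found.
- **Statistical methods {20a}:** for 30-day mortality, "we will use the unadjusted hazard ratio determined from Cox regression to estimate the mortality rate ratio between the treatment groups". Adjustment is conditional, and the clause that allows it begins: "If we detect any imbalances in potential confounders at baseline (such as age, sex, severity of illness, study site), then an adjusted Cox model will".
- **Methods for additional analyses {20b}:** secondary analyses repeat the primary one, "adjusting for the confounding factors of gender, hospital location, age at randomization and any other confounder as deemed appropriate".

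Study setting {9} names 20 hospitals: 15 in the Clinical Information Network and five others.

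**The concern.** A separate permuted-block list for each hospital is randomisation stratified by hospital. Section {20a} counts study site among the factors examined at baseline, so on the protocol's own usage the denial in {20b} is a misstatement.

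The analysis then does not follow the design. Blocking within site balances the arms on site. If hospitals differ in mortality, the treatment estimate varies less from one hypothetical repetition of the trial to the next than an unadjusted model assumes. Leaving out a prognostic factor also pulls the Cox log hazard ratio towards zero. Both effects make the primary test conservative.

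The conditional clause does not repair this. It brings site in when site is imbalanced, which is what the randomisation was built to prevent. What matters for the analysis is whether site predicts death, not whether it is unbalanced. At stake are a little power and a nominal 5% test that runs somewhat below 5%.

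**Working it through.** **1. Reproduce the planned size.** Inputs from Sample size {14}: 20% against 15% mortality, 85% power, two-sided 5%, 5% loss. The pooled-variance formula for two proportions gives 1,036 per arm, and 1,036 / 0.95 = 1,091, against 1,090 stated. With 1,090 × 0.95 = 1,035.5 per arm, power is 85.0%. The plan's figure reproduces. On the Cox scale these risks imply HR = ln(0.85) / ln(0.80) = 0.728. Schoenfeld's formula needs 358 deaths for 85% power; 2,180 × 0.95 × 0.175 = 362 are expected after losses, giving 85.5%.

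**2. Can the imbalance clause bring in site?** The average hospital has 2,180 / 20 = 109 patients. If the largest block is 8 (assumed; sizes are not given), the arms within a hospital differ by at most 4 patients. Site will hardly ever look imbalanced.

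**3. Simulate the design.** The set-up was 20 sites of 109 patients, blocks of random size 2 to 8 within site, exponential survival, censoring at day 30, 20% control mortality and no losses. Site effects were normal on the log hazard. Their SD is an assumption, because the document gives no between-site variation. For scale, take a median hospital at 20%. The 10th to 90th percentile of control mortality is then 1 − exp(−0.223 × exp(±1.28 × SD)): about 14% to 28% at SD 0.3, 11% to 35% at SD 0.5 and 8% to 46% at SD 0.8.

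There were 6,000 runs with no treatment effect and 3,000 at HR 0.728. Paired entries are unadjusted / site-stratified Cox.

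| Site SD | Model SE ÷ true SD, unadjusted, null | Type I error | Mean log HR at HR 0.728 | Mean model SE at HR 0.728 | Power |
|---|---|---|---|---|---|
| 0 | 0.99 | 5.1% / 5.0% | −0.3182 / −0.3182 | 0.1038 / 0.1038 | 86.7% / 86.5% |
| 0.3 | 1.00 | 4.6% / 4.8% | −0.3140 / −0.3165 | 0.1037 / 0.1038 | 86.3% / 86.6% |
| 0.5 | 1.04 | 4.0% / 4.5% | −0.3106 / −0.3179 | 0.1040 / 0.1041 | 84.7% / 85.9% |
| 0.8 | 1.06 | 3.8% / 4.9% | −0.2949 / −0.3144 | 0.1041 / 0.1043 | 81.6% / 84.7% |

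Monte Carlo error is about 1% on the SE ratios and √(0.05 × 0.95 / 6,000) = 0.3 points on type I error, so nothing can be read into SD 0.3. The 86.7% at SD 0 matches the two-proportion power for 1,090 per arm without losses, also 86.7%.

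**4. Repeat with fixed blocks of four.** At SD 0.3, 0.5 and 0.8, unadjusted type I error was 5.1%, 4.8% and 3.7%. Power was 83.2% against 83.6%, 82.8% against 84.1%, and 79.2% against 82.7%. Absolute power is lower here than in step 3, so only comparisons within a run should be read. The gaps are 0.4, 1.3 and 3.5 points, against 0.3, 1.2 and 3.1 in step 3.

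**5. Where the gain comes from.** At SD 0.8 the mean estimate over the model SE is 0.2949 / 0.1041 = 2.83 unadjusted and 0.3144 / 0.1043 = 3.01 stratified. The denominators are almost equal. The stratified model gains because its log hazard ratio is less attenuated and its SE matches its true variability.

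**The case against.** **Site is not a patient characteristic.** The sentence in {20b} could be read as referring to patient-level factors only. That would excuse the wording if {20a} did not itself list study site among baseline factors. The misstatement stands, though it is a matter of one clause.

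**A reader might infer that the confidence interval is too wide and that stratifying would narrow it, or that a stated number of patients is wasted.** Neither is supported. The model SEs agree to within 0.0002 in every row above, and at SD 0.5 with fixed blocks they are 0.1076 and 0.1077. Patient equivalents come from 1 − Var(site risk) / {p(1 − p)}, which applies to a difference in proportions and not to the Cox log hazard ratio that {20a} specifies.

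**A reader might infer that validity is threatened.** It is not. The error is conservative, and an unadjusted analysis specified in advance is defensible after site-blocked randomisation, only less efficient. This stands in full.

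**A reader might infer that site is ignored throughout.** It is not: {20b} adjusts the secondary analyses for hospital location, and {20a} names site in the conditional model. A site-adjusted mortality estimate is therefore likely to be reported, but not as the primary result.

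**The size rests on an assumption.** This also stands. Nothing in the document fixes between-site variation; that county and national referral hospitals differ in mortality is plausible inference.

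**Conclusion.** The point holds as a minor one. The denial of stratification in {20b} contradicts {16a} and {16b}, and the primary model omits the factor by which patients were randomised, under a condition that blocking makes very unlikely to be met for site.

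The size depends on the assumed site SD: nothing at 0, negligible at 0.3, about 1.3 points of power with type I error of 4 to 5% at 0.5, and about 3 points with type I error near 3.7% at 0.8. The last case needs very strong differences between hospitals. These figures also assume equal site sizes, 20 sites (the Figure 1 caption adds up to 18) and proportional hazards within site.

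**What to change.** 1. In {20b}, state that randomisation was stratified by site.
2. In {20a}, make the primary analysis a Cox model stratified by site, without a condition, and remove site from the imbalance clause. Keep the unadjusted hazard ratio as a sensitivity analysis.

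**Cost.** No new data are needed, the sample size does not change, and with no site variation the loss is nil within simulation error (86.5% against 86.7%). Two costs are real. The hazard ratio becomes conditional on site, a slightly different quantity from the unadjusted one, and the report should say so. The timing also matters: Study status records that recruitment ended on 30 June 2024, the trial is open label, and {21b} sends interim mortality comparisons to the monitoring board and the steering committee. A change of primary model therefore needs a documented amendment, reviewed as {25} requires, before comparative results are seen, with a record of who has seen interim results. If that is no longer possible, keep the unadjusted analysis as primary, correct {20b}, and report the site-stratified Cox model as a labelled sensitivity analysis.

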## Introduction

### Background and rationale {6a}

Community acquired pneumonia (CAP) is a common cause of illness and death among adults in Kenya and other low and middle-income countries (LMICs)
^
1
^. The pattern of CAP in sub-Saharan Africa differs from that in other regions due to higher prevalences of coinfections like pulmonary tuberculosis and HIV and differences in risk factors for severe disease in this population compared to others
^
2
^.

Inflammation plays an important role in the pathophysiology of pneumonia with elevated levels of inflammatory cytokines and infiltration of interstitial lung tissue with various inflammatory cells being observed in patients with severe disease
^
3
^. Dysregulated inflammation results in a sepsis-like syndrome with eventual organ dysfunction in severe cases
^
4
^.

Corticosteroids have a role in improving patients outcomes in CAP by modulating the release of inflammatory mediators such as cytokine and reducing pulmonary inflammation
^
5
^. While previous data on the effect of corticosteroids in the management of CAP have been inconclusive
^
6–
9
^, data from the RECOVERY trial during the COVID-19 pandemic
^
10
^ and other studies such as the ESCAPe
^
11
^ and CAPE COD
^
12
^ trials have demonstrated a beneficial effect of adding corticosteroids to the management of patients admitted with severe CAP. Consequently, several systematic reviews and metanalyses now report corticosteroids have beneficial effects in reducing progression to invasive ventilation, duration of hospital stay and mortality
^
13–
16
^.

These studies are however potentially not applicable to settings such as Kenya for the following reasons; a) mortality in this setting is ~30%, which is much higher than that observed in studies in high income settings, b) patients in our setting are younger (35–50 years) compared to average age of 65 years in other settings c) the prevalence of comorbidities (e.g. HIV and TB) in patients with CAP in LMIC settings is different. Without evidence from a sub-Saharan African population, questions remain on the effectiveness of adjunctive corticosteroids in the management of patients admitted with severe CAP in the region.

 We are conducting a pragmatic randomized controlled open-label clinical trial to test if there is a survival benefit in the use of adjunctive low-dose corticosteroid therapy in patients admitted to hospital with CAP.

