## Trial design {8}

We will conduct a pragmatic open label randomized controlled clinical trial. Eligible participants will be recruited from the in-patient adult medical wards of the participating hospitals. Patients admitted to the general wards as well as the High Dependency Units (HDU) and Intensive Care Units (ICU) will be eligible to join the trial and will be identified by the attending clinician and a study clinician.

Participants enrolled into the trial will be randomized 1:1 to either receive standard of care for CAP or standard of care plus a 10-day course of low-dose oral corticosteroids. A subset of all recruited participants, about 50 per trial arm, will be further randomized to have a blood draw at four timepoints during their participation. For these participants, a 10 ml blood sample will be collected at enrollment, 24, 48 and 72 hours after enrollment for an immunology sub study.

All participants will be followed up to their 30
^th^ day after enrollment to determine their vital status. The median duration of hospital admission for patients with CAP in the participating hospitals is 4 days, therefore having the primary outcome ascertained at 30 days is unlikely to result in misclassification of patients where some are recorded as being alive only to die a few days later.

Being a pragmatic trial, the study will not interfere with any procedure, investigations, or treatments that the attending clinicians administer to participants. However, all treatments received will be recorded.

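### Stratified results are presented on condition of a significant interaction with an unspecified set of baseline variables, so subgroup results are selected by p-value

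*Protocol article*

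**What the plan says.** The protocol article has one sentence on subgroups, in Methods for additional analyses {20b}: "stratified analyses will be presented if there is significant evidence of interaction by any of the baseline variables". It sets a condition (a significant interaction) and leaves the candidate variables open.

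Background and rationale {6a} gives three reasons why earlier steroid trials may not carry over to Kenya. Local mortality is higher, patients are younger, and "the prevalence of comorbidities (e.g. HIV and TB) in patients with CAP in LMIC settings is different". Eligibility criteria {10} keeps patients with HIV in the trial. The background also describes the earlier benefit as having been seen in severe pneumonia, but severity is not one of the three listed reasons. Severity appears in Statistical methods {20a} only as an example of a possible baseline imbalance, and the article defines no severity measure.

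Sample size {14} plans for the overall comparison. It assumes that "30-day mortality in the control arm of the trial will be 20% and that 30-day mortality in the intervention arm will be 15"%, and it gives "a sample size of 1,090 patients per study arm (total 2,180 patients, ~ 390 deaths".

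**The concern.** A rule that shows a stratified result when its interaction test is significant can go wrong in two directions. If many variables are screened, some will pass by chance, and those are the ones readers will see. If the trial is sized for the overall effect, most true interactions of moderate size will fail the test, and the stratum estimates will not be shown. The published set of subgroup results would then be shaped by p-values rather than by the questions asked in advance.

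This matters here because the case for running the trial rests on differences in the patients. A reader who wants to know whether the result looks similar in people with and without HIV, or in younger and older adults, needs the estimates and intervals even when the interaction test is not significant. A non-significant test with wide intervals tells that reader something; an absent result does not.

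**Working it through.** **Inputs from Sample size {14} and Trial design {8}.** Mortality 20% and 15%; two-sided 5% ("with a 2-sided type 1 error rate of 5"%); power 85% ("will achieve statistical power of 85"%); 5% loss ("Allowing for 5% loss to follow-up"); 1,090 per arm; 1:1 allocation ("Participants enrolled into the trial will be randomized 1:1").

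**Inputs not in the article, so assumed.** Interaction tests at two-sided 5%; independent tests; *k* = 4 to 20 variables tested; binary subgroups holding a share *f* = 10% to 50% of the deaths.

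**Step 1: reproduce the plan's figure.** With the pooled-variance formula for two proportions,

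n = [1.96·√(2 × 0.175 × 0.825) + 1.036·√(0.20 × 0.80 + 0.15 × 0.85)]² / 0.05² = 1,036 per arm.

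Dividing by 0.95 gives 1,091, against the stated 1,090. Power with 1,090 × 0.95 = 1,035.5 per arm is 85.0%. The sample size reproduces, and this point does not touch it.

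Expected deaths are 1,090 × (0.20 + 0.15) = 381.5, or 362 after 5% loss. The article states about 390. Both 362 and 390 are used below.

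**Step 2: chance of at least one false interaction.** With no true interaction this is 1 − 0.95^k.

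| k | 4 | 10 | 20 |
|---|---|---|---|
| Probability | 18.5% | 40.1% | 64.2% |

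**Step 3: power to flag a real interaction.** The planned rates imply an overall hazard ratio of ln(0.85)/ln(0.80) = 0.728. Take an interaction of that same size, for example a hazard ratio of 0.73 in one level and 1.00 in the other. With *D* deaths in total, the standard error of the log ratio of hazard ratios is

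SE = √(4/(D·f) + 4/(D·(1 − f))),

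and power is Φ(|ln 0.728|/SE − 1.96), plus a negligible opposite tail. For D = 362 and f = 0.5, SE = 0.210, and 0.317/0.210 − 1.96 ≈ −0.45, which gives 33%.

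| Share of deaths in subgroup | SE, D = 362 | Power, D = 362 | Power, D = 390 | Ratio needed for 80% power, D = 362 |
|---|---|---|---|---|
| 50% | 0.210 | 33% | 35% | 0.56 |
| 30% | 0.229 | 28% | 30% | 0.53 |
| 20% | 0.263 | 23% | 24% | 0.48 |
| 10% | 0.350 | 15% | 16% | 0.38 |

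The last column is exp(−2.80 × SE). A true difference as large as the whole planned effect would therefore fail the test, and under the stated condition go unpresented, about 65% to 85% of the time. Whether 362 or 390 deaths are used makes little difference.

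**The case against.** The strongest reply is that the sentence does not say that other subgroup results will be withheld. It says when stratified analyses will be presented, and is silent on the rest. That is correct: exclusivity is an inference. It is nevertheless the natural reading of a stated condition, and the article contains no commitment that points the other way.

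A second reply is that a named subgroup list, an interaction significance level and multiplicity handling normally belong in the statistical analysis plan, which is not shown. This also stands, and their absence is not counted here. What remains is the condition itself, which an analysis plan would have to override rather than fill in.

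Third, requiring an interaction test before reading stratum-specific effects is a conventional guard against over-interpretation. That supports doing the test and giving it weight. It does not support making display of the estimates depend on the result.

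Fourth, a reader might infer that the plan conceals the very results that motivated the trial, or that it leaves a safety question unanswered. The documents do not support that. The background says that the population differs from earlier ones, which the overall Kenyan result addresses directly. It does not say that age, HIV or TB modify the steroid effect, and no objective or outcome is a subgroup effect. Severity is not among its listed reasons, and nothing in the article identifies these subgroups as the main safety concern.

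Finally, a fixed list does not remove false positives. Four tests at 5% still carry an 18.5% chance of at least one if independent, and power is unchanged. The gain is that nothing is shown or left out because of its p-value.

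**Conclusion.** The point holds as a defect in a stated reporting rule, not as a claim that results will be suppressed or that detail is missing. Followed as written, {20b} selects stratified results by significance from an unlimited set of candidates. The probability of at least one chance finding is about 18.5% to 64% for 4 to 20 variables. Power to flag an interaction equal to the whole planned effect is about 15% to 35%.

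These figures rest on assumptions that the article does not supply: the number of variables, a 5% interaction level, independence, and the subgroup's share of deaths. Correlated variables would lower the false-positive figures. The direction of the conclusion does not depend on any single choice within the ranges shown.

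The primary analysis and sample size are unaffected. What is at stake is how readers judge whether the result applies across the patients enrolled.

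**What to change.** Replace the conditional sentence with a short fixed list: age, HIV status, known or suspected TB at admission and, if a baseline severity measure was recorded, severity. For each:

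- report the effect estimate with its 95% confidence interval in every level, and the interaction test, whatever the p-value;
- report how many participants have missing subgroup status, since data come from medical records and the article rules out imputation;
- interpret the set without claiming control of the false-positive rate across subgroups.

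Label any other interaction exploratory and state how many were examined.

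Study status gives 30 June 2024 as the end of recruitment, and the trial is open label. State the date on which the list was fixed relative to anyone's access to outcome data by arm, so that readers can judge how far it counts as pre-specified.

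The cost is revised wording, a little more analysis and one forest plot, with wide intervals in small subgroups. No new patients are needed. That HIV and TB status can be taken from the admission record is an assumption to confirm.
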